## Abstract

**Background:**

Digital media-use disorders (DMUD) in adolescents are a rising phenomenon associated with psychological distress, comorbid mental disorders, and high burden on affected families. Since the ICD-11 introduced criteria for gaming disorder, these can now be transferred to describe additional DMUD associated with social media platforms and streaming services. Most evidence for effective treatments comes from cognitive-behavioral therapy (CBT). However, interventions based on theoretical models for adolescents and their parents are widely missing, leading to a significant clinical gap.

**Methods:**

Res@t digital (Resource-Strengthening Training for Adolescents with Problematic Digital-Media Use and their Parents) is the app-based translation of the first model-based digital intervention for adolescents with DMUD and their parents based on CBT. It comprises separate but content-related modules for adolescents (Res@t–A) and parents (Res@t–P), applying multimodal techniques. The effectiveness of Res@t will be evaluated within a multicenter cluster-randomized controlled evaluator-blinded pre–post follow-up trial with the waitlist control group (CG). In addition to the Res@t program in the intervention group, both groups will receive treatment as usual within primary child and adolescent psychiatric/psychotherapeutic healthcare. The primary outcome addresses DMUD symptom reduction after 10 weeks. Secondary outcomes are related to a reduction in psychological and family-related problems and an increase in parental self-efficacy. All outcomes will be assessed using standardized self-report measures. A total of 1,334 participating adolescent–parent dyads from a large clinical network throughout Germany are planned to be included in the primary analyses based on an intention-to-treat approach, applying linear mixed models.

**Discussion:**

Assuming superiority of Res@t over the control condition, the intervention has the potential to provide evidence-based treatment for a significant number of help-seeking families, supporting local healthcare structures and resources. It is a promising program for practicable implementation and flexible use in different settings.

**Clinical trial registration:**

https://drks.de, DRKS00031043.

## Introduction

1

The digital entertainment and media market industries belong to the fastest-growing businesses in the world (1). In 2022, revenue from digital games amounted to 184 billion U.S. dollars with mobile games accounting for 50% of the global gaming market (2). During the last decades, improved design mechanisms and broad availability led to increased usage frequency and duration worldwide over all age groups (3). During the COVID-19 pandemic, this development was fostered by contact restrictions, quarantines, and the closure of schools and leisure facilities, especially for children and adolescents (4–6). The majority of German children and adolescents use digital media on a regular basis from several times a week to daily, including social media (SM, more than 90%), video streaming (*VS*) services (more than 80%), and digital games (more than 70%) (7).

For some users, frequent digital media use as a leisure activity can turn into problematic patterns, resulting in severe negative personal, family, social, educational, and work-related sequelae with significant subsequent costs to healthcare and economic systems (8). Recent meta-analyses estimated the worldwide prevalence of problematic gaming between 3.1 and 3.3% (9, 10) and problematic SM use at 5% (11) with a peak during adolescence. Much less research has been conducted on problematic *VS*, although similar addiction-promoting mechanisms are applied to increase user bonding (12). Most associated research has focused on binge-watching, i.e., the consumption of several (television) series episodes in a row (13, 14). However, the series resembles only a small subentity of *VS* services. A representative study on German adolescents estimated the prevalence of pathologic *VS* at 4.7% in frequent (at least weekly) *VS* users (15).

Adolescents are particularly at risk for behavioral addictions including problematic gaming due to neuronal remodeling processes with a mature reward system, on the one hand, and a cognitive-control system that is still in development on the other hand (16, 17).

As the first behavioral addiction purely associated with digital media, problematic (online or offline) gaming has been included in the current (11th) version of the International Classification of Diseases (ICD-11) as *Gaming Disorder* (GD, 6C51) (18). Four criteria have been defined for diagnosing GD which must usually be present for the past 12 months: loss of control over the temporal and situational use of digital games, increased prioritization of digital gaming over alternative activities, continued or increased gaming despite negative consequences, and the occurrence of significant impairments in important areas of functioning. At the current state, other digital-media-related disorders (DMUD), such as *Social Media Use Disorder* (SMUD) or *Video Streaming Disorder* (VSD), can be classified under the umbrella *Other specific disorders due to addictive behaviors* (GC5Y), applying comparable criteria as for GD (19). Affected individuals who do not (yet) fulfill all criteria of addiction can be classified under *Hazardous Gaming* (HG, QE22) or *problems with other specified health-related behaviors* (QE2Y). The latter can include Hazardous Social Media Use (HSMU) and Hazardous Video Streaming (HVS). Disordered or hazardous usage patterns can be summarized as Problematic Gaming (PG), Problematic Social Media Use, or Problematic Video Streaming (PVS).

The etiology of DMUD can, e.g., be described by the *Triad Model of Addiction* by Kielholz & Ladewig (20). This biopsychosocial model describes an interaction of personal, social, and agent-related factors. It employs mechanisms of learning, stress management (21), and information processing and can be comprehensively applied to DRMD in adolescents. For more details, please refer to the study by Paschke et al. (22).

If DMUD remains untreated, there will be a high risk of chronicity with severe psychological consequences, repeated hospitalizations, and failure to fulfill necessary developmental tasks (e.g., no school qualifications, no education) with negative effects on the mental and physical health of the affected person and high costs for society. The best effects on symptom reduction have been shown for cognitive-behavioral therapy (CBT) (23). However, model-based and evidence-based treatment programs, addressing adolescents and their parents, are currently not available (24–26).

### Aim of the study and hypotheses

1.1

The present study aims to evaluate the effectiveness of a new model-based standardized online intervention program, the Resource-Strengthening Training for Adolescents with Problematic Digital-Media Use, and their Parents (Res@t digital) in an outpatient setting. The Res@t digital intervention group (IG) will be compared with a waiting control group (CG). The IG will receive the Res@t digital intervention, and both groups will receive treatment as usual (TAU) during the study period. The waitlist CG will be offered access to the intervention after individual data collections are completed. It is hypothesized that Res@t digital + TAU is superior to TAU only and will lead to a decrease in adolescent DMUD (i.e., GD, SMUD, or VSD) symptoms. In the case of an adolescent being affected by more than one DMUD or hazardous use pattern, the clinician will identify the most prominent phenomenon that will be focused on within the targeted intervention. Moreover, Res@t digital will reduce mental-health-related problems in adolescents and increase parental self-efficacy.

There are three primary hypotheses structured hierarchically which address the one most prominent DMUD or hazardous use pattern in the individual adolescent identified by the clinician (i.e., PG, PSMU, or PVS). This is referred to the term “specific” DMUD:

First primary hypothesis: Res@t + TAU reduces symptoms of specific DMUD in adolescents compared with TAU, measured as change from screening to post-intervention. Second primary hypothesis: Res@t + TAU reduces symptoms of specific DMUD in adolescents assessed by their parents compared with TAU, measured as change from screening to post-intervention. Third primary hypothesis: Res@t + TAU reduces symptoms of specific DMUD in adolescents assessed by their treating clinicians compared with TAU, measured as change from screening to post-intervention.

To the best of our knowledge, although positive effects of online interventions have been repeatedly suggested to fill substantial treatment gaps for mental health issues in adults (27–29) and adolescents (30–32) including addictive behavior (33–35), no comparable intervention for adolescents with DMUD and their parents is available yet. Therefore, Res@t strives to close a significant void.

## Methods and analysis

2

### Study design

2.1

The current study is a multicenter, prospective, cluster randomized-controlled, observer-blind clinical trial on the effectiveness of Res@t regarding symptom reduction in adolescents with DMUD. A two-arm study design will be applied with an IG and a waitlist CG with pre–post follow-up assessments. All patients will receive surveillance by a child and adolescent psychiatrist and psychotherapist who offers TAU in regular treatment parallel to the study.

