### Blinding

2.7

Practitioners will be informed whether their recruitment site has been assigned to IG or CG at the beginning of the study. Once a patient has been identified to be eligible for study participation and the family gave informed consent to participate, the practitioner will individually inform about the assignment to IG or CG. Evaluating data analysists at IMBE will be blinded and will receive blinded datasets only.

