Children and adolescents will be classified as disordered if the cutoffs for both factors are reached and the time criterion is met. Reaching the cutoff of CBS only suggests hazardous media use. In the clinical context, the DMUD test battery has been regularly used and could prove to be helpful in assessing potential symptom changes during therapy.

Additionally, each treating clinician will assess symptom expression, rate fulfillment of the ICD-11 criteria (based on criteria of GD), and diagnosis of a potential specific DMUD. They will be provided with a digital criterion checklist including examples to enhance interpretation based on ICD-11 suggestions, the clinical interview guideline of the Gaming Disorder and Hazardous Gaming Scale (GDHGS) (69), and clinical expert experience.

In the case of the diagnosis of more than one DMUD, the clinically most prominent one (i.e., by total rating scores and clinical evaluation) will be defined as the main DMUD. This will be addressed during intervention and used as a primary outcome, which was assessed during enrollment, at post-intervention, and follow-up. The differences between screening and post-intervention total scale scores will be investigated primarily.

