## Limitations

4

A cluster-randomized design was chosen to exclude contamination effects on TAU within IG and CG. However, by involving practitioners actively in the study and providing structured diagnostic tools for the assessment of DMUD, it cannot be ruled out that TAU is altered by an increased awareness of the clinicians. This effect might be stronger in recruitment sites that are allocated to CG as child, and adolescent psychiatrists and psychotherapists strive to address detected problems, where no immediate additional support is available. More attention to the CG compared with the IG would result in a potential reduction in the overall outcome effect. Measures taken against this will include proper instruction of recruiting practitioners. Moreover, the cluster-randomized design does not allow initial sample stratification, e.g., regarding the type of DMUD, sex, age, and single versus dyad study participation. However, the number of recruitment sites is aimed to be so high that these variables should be distributed randomly. Another potential drawback of cluster randomization is that the waiting CG will get access to the intervention after their individual data collection but not after full data collection. Based on the feedback from recruiting clinicians, waiting times of several months up to a year in that case would not have been acceptable. Clinicians will be instructed to not to alter TAU based on their experiences with Res@t digital. However, contamination effects on TAU cannot be ruled out.

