## Conclusion

5

Res@t digital is the first model-based and app-based intervention that addresses the vulnerable group of adolescents with DMUD or hazardous use patterns and a respective parent in order to reduce symptoms and negative sequelae, prevent chronification, and foster the mastering of developmental tasks. After standardized diagnosis, treatment effectiveness will be evaluated by applying a multicenter cluster-randomized pre–post follow-up waitlist control group design with evaluator blinding within the primary clinical care setting. It will be tested if Res@t digital is feasible for and effective in outpatients who receive the intervention in addition to TAU compared with the control group with TAU only. By selecting a study setting within primary clinical care, optimal patient security can be assured, blended-therapy approaches are made possible, and important implementation factors can be accounted for to increase acceptance and accessibility from the very beginning. If effectiveness is shown, Res@t will be made available for long-term perpetuation, considering practicability and potential independence of local care structures and cost-effectiveness.

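### Section 2.1 calls the trial observer-blind, but section 2.7 blinds only the data analysts, and no primary outcome has a rater described as blinded

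*Protocol article*

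**What the plan says.** Section 2.1 of the protocol article calls the study a "multicenter, prospective, cluster randomized-controlled, observer-blind clinical trial on the effectiveness of Res@t". The abstract (Methods) uses "multicenter cluster-randomized controlled evaluator-blinded", and the conclusion (section 5) refers to a "waitlist control group design with evaluator blinding within the primary clinical care setting".

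Section 2.7 (Blinding) says: "Practitioners will be informed whether their recruitment site has been assigned to IG or CG at the beginning of the study". Once a family is eligible and has consented, "the practitioner will individually inform about the assignment to IG or CG". The only blinded role it names is that of the analysts at the biometry institute.

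The third primary hypothesis (section 1.1) concerns symptoms as assessed by the treating clinician. Section 2.10.1 confirms the task: "each treating clinician will assess symptom expression, rate fulfillment of the ICD-11 criteria". Treating practitioners also recruit (section 2.2), apply the clinical-examination criterion for eligibility (section 2.3) and identify the most prominent disorder when there is more than one (sections 1.1 and 2.10.1). That choice determines which scale serves as the primary outcome.

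On balance between arms, section 4 (Limitations) says of disorder type, sex, age and single versus dyad participation that "the number of recruitment sites is aimed to be so high that these variables should be distributed randomly".

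**The concern.** An observer-blind trial is one in which whoever observes and scores the outcome does not know the arm. Analysts do not observe the outcome. If the rater knows the allocation, the label claims a protection that the trial does not have, and a reader would give a clinician-rated result more weight than it can bear. Hypothesis 3 is the only one of the three rated by a professional, so it is the natural candidate to be read as independent confirmation of the self- and parent reports.

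Recruitment raises a second, related issue. Sites are randomized and told their arm, and only then recruit. Selection made with the arm known can differ systematically between arms. The section 4 argument from the number of sites concerns chance imbalance and does not address this. Section 4 discusses altered usual care and contamination, but neither unblinded rating nor recruitment after allocation.

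**Working it through.** **1. Who knows the arm**

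| Role | Task | Status in the protocol article |
|---|---|---|
| Adolescent | Rates hypothesis 1 | Told the arm after consent (2.7) |
| Parent | Rates hypothesis 2 | Told the arm after consent (2.7) |
| Treating clinician | Recruits, confirms eligibility, identifies the main disorder, rates hypothesis 3 | Knows the site's arm from study start (2.7) |
| Data analyst | Analyses the data | Blinded (2.7) |

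Section 2.6 sets clinical diagnosis and the post-treatment evaluation apart from the questionnaires that are delivered online without the clinician. No independent or blinded outcome assessor is described. Concealing site identity from the allocating statistician (section 2.5) protects the assignment of sites; it does not blind a rater.

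**2. Room for selection**

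Section 2.4 plans to screen 13,340 patients, with 20% affected and 50% participating: 13,340 × 0.20 = 2,668 eligible, and 2,668 × 0.50 = 1,334 enrolled. Half of the eligible patients are expected not to take part, and every recruiter knows the arm.

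**3. The plan's own power figure**

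Inputs from section 2.4: 667 per group, 40% dropout before week 10, 50 sites (25 per arm), ICC 0.005, coefficient of variation 0.4, d = 0.2, two-sided 5%.

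- Analysed per arm: 667 × 0.6 = 400. Mean cluster size: 400 / 25 = 16.
- Design effect: 1 + ((CV² + 1) × m − 1) × ICC = 1 + (1.16 × 16 − 1) × 0.005 = 1.0878.
- Effective size per arm: 400 / 1.0878 = 367.7.
- Noncentrality: d × √(367.7 / 2) = 0.2 × 13.56 = 2.712.
- Power: Φ(2.712 − 1.96) = 77.4%, which matches the stated 77%.

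**4. Illustration: bias in the clinician rating and no true effect**

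The article gives no size for rater bias, so the range is an assumption. With noncentrality = 13.56 × bias (in SD), the probability that the third test, taken alone, is significant in favour of the intervention is:

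| Assumed bias (SD) | Probability |
|---|---|
| 0 | 2.5% |
| 0.05 | 10% |
| 0.10 | 27% |
| 0.15 | 53% |
| 0.20 | 77% |

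**5. Effect of the hierarchy**

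Section 2.12 makes hypothesis 3 confirmatory only after hypotheses 1 and 2 are significant. If only the clinician rating is biased, the test of hypothesis 1 gates it, and the confirmatory error for hypothesis 3 stays at or below 5%. If all three ratings carry a 0.1 SD bias, the probability that all three tests succeed lies between 0.273³ ≈ 2% (independent tests) and 27% (perfectly correlated tests).

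**6. Covariates**

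Section 2.10.3 says that sociodemographic variables, age and sex/gender among them, will enter as covariates. The primary model in section 2.12 lists group, disorder type, site size, location, random effects and the baseline score, but neither age nor sex.

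**The case against.** The best defence is that families cannot be blinded when an app is compared with a waitlist, and that the first two outcomes are collected online without clinician involvement. Both points are fair. They explain why the trial is open; they do not justify the observer-blind label.

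Several stronger readings are tempting, and the article does not support them:

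- *The evaluator-blinded label is false.* Section 2.7 describes the analysts as evaluating, and section 2.11 refers to an evaluation team, so the abstract and conclusion can mean the analysts. The term is ambiguous; the clear contradiction is with section 2.1.
- *Differential enrolment goes wholly unadjusted.* The primary model already contains the baseline symptom score and the disorder type. Hazardous or pathological status rests largely on cutoffs of the same scales, so it would add little.
- *The clinician has free choice of patients and scale.* Eligibility also requires a questionnaire cutoff (section 2.3). The main disorder rests partly on total scores, needs choosing only when there is more than one, and is settled at enrolment (section 2.10.1). Discretion is limited, though not removed.
- *Table 2 contradicts section 2.7 by placing allocation after baseline.* It can be read as a patient timeline, since families learn their arm after consent.
- *The clinician result will be reported as blinded confirmation.* Nothing in the article says so, and section 4 asks for caution where the ratings diverge.

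**Conclusion.** The label in section 2.1 is wrong as written. By the article's own account the trial is open to patients, parents and treating clinicians, only the analysts are blinded, and all three primary outcomes are rated by people who know the arm. Hypothesis 3 therefore cannot serve as independent blinded confirmation. Recruitment after the site's arm is known is a separate limitation, and a large number of sites does not remove it.

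The 27% and 77% figures rest on an assumed bias of 0.1 or 0.2 SD, no true effect, the planning values of section 2.4, and the third test taken alone. A reader might take them for the trial's confirmatory error rate. They are not: the hierarchy lowers that rate, and holds it at or below 5% if only the clinician rating is biased. They do show that a bias as large as the planned effect (0.2) would make the third test significant as often as the planned effect would.

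The disagreement over age and sex between sections 2.10.3 and 2.12 is an inconsistency to resolve. It does not show that the two variables are ignored.

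**What to change.** - Section 2.1: replace observer-blind with open-label with blinded data analysts, or state who rates the clinician outcome blind to allocation. Clarify evaluator-blinded in the abstract and section 5 in the same way.
- Section 4: state that hypothesis 3 rests on an unblinded treating-clinician rating and is not independent blinded confirmation. State also that patients are recruited after the site's allocation is known, and that the number of sites does not protect against this.
- Sections 2.10.3 and 2.12: reconcile them by adding age and sex as fixed covariates to the primary model, alongside the baseline score and disorder type already there.
- Optional: a sensitivity analysis in which the target scale is chosen by a fixed rule from the screening scores. Table 2 schedules all three scales at screening, week 10 and week 20.

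The cost is wording, two covariates already collected and, if wanted, one further analysis. No new data are needed. The trial gives up a favourable design label.

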### Study sample and setting

2.2

Adolescents aged 10 to 19 years (based on the WHO definition of adolescence) and their respective parents, i.e., caregivers, will be recruited for the study by their child and adolescent psychiatrists and/or psychotherapists. Recruitment sites will include 10 outpatient departments of participating clinics (five university hospitals, five large care clinics) and approximately 40 practices throughout Germany (coordinated via the Professional Association for Child and Adolescent Psychiatry, Psychosomatics, and Psychotherapy in Germany e.V., BKJPP).

All eligible recruitment sites will be assigned randomly to IG or CG. Sites randomized to CG will have the opportunity to use Res@t after study recruitment and follow-up are completed.

In addition to introducing the study in regular appointments, advertisements will be carried out via five health insurance companies and the German Society for Child and Adolescent Psychiatry, Psychosomatics, and Psychotherapy (DGKJP) who support the study. Adolescents and parents who are interested in the study will be referred to participating clinics and practices, an appointment for screening and diagnosis will be made, and they will be informed about study details.

Screening for DMUD will take place for all patients within regular child and adolescent psychiatric diagnostics. If a DMUD is confirmed during clinical examination, adolescents and parents will be informed verbally and in writing about the study purpose and procedure including intervention, assessments, and recruitment-site-associated randomized group allocation. Further information concerns confidentiality and data protection procedures including pseudonymization, anonymous data storage at the study center (German Center for Addiction Research in Childhood and Adolescence, DZSKJ, University Clinic Hamburg-Eppendorf, UKE) for 10 years after study completion, possible advantages and disadvantages of participation, and the option to withdraw from the study at any time and without any given reason. Before study enrolment, adolescents and parents give their informed consent and receive all necessary documents on the study.

Since all participants are patients in regular treatment, they will not be financially compensated. However, patients will be offered a voucher for a large selection of online shops as incentive for full questionnaire completion with graded values according to assessment points.

Patient recruitment (first patient in to last patient out) is planned from January 2024 to May 2025. This includes a recruitment period of 12 months and a treatment and follow-up period of 17 months in total.

